#### Sample size

The sample size for the trial is based around the primary outcome measure of the total HRQL score taken from the UFS-QoL questionnaire, and is informed by the results of the pilot study at St George’s Hospital [11]. The mean difference seen here from the 118 patients who provided questionnaire responses at twelve months was 12 points in favour of myomectomy, with a standard deviation of 22 points (using an analysis of covariance approach). This is equivalent to approximately 0.5 standard deviations (rounded downwards to be conservative). To detect a difference of this size (a moderate effect [14]) with 90% power (*P* = 0.05) would require 86 patients in each group (172 in total). Whilst the number of women expected to become pregnant before the primary outcome time of two years is expected to be low (10% or less), some provision needs to be made for these women as not all questions on the UFS-QoL will be still relevant. Additionally, a further 10% has also been added to account for loss to follow-up (including withdrawals). Thus, the final target sample size has been inflated to 216 patients.

### Data management and quality assurance

#### Data protection

Data will be stored and analysed in accordance with the Data Protection Act 1998, plus any other relevant legislation. Completed forms returned to the trials office will be stored securely in a locked filing cabinet within a safe haven office. There is a strictly enforced hierarchical access policy which ensures that research staff (including those at local sites) only have access to the electronic information which is necessary for them to perform their duties, for example, allowing patients to be contacted for follow-up or allowing data checks and validation.

#### Confidentiality

Personal and sensitive data will be collected directly from trial participants and their hospital notes. Participants will be informed about the transfer of this information to the FEMME study office at Birmingham Clinical Trials Unit (BCTU) and asked for their consent. With the patient’s consent, their full name, date of birth, NHS or Community Health Index number, address, postcode, hospital number, GP details, and the participant’s telephone number and e-mail address will be collected at trial entry. This will allow direct contact with the participant and enable tracing of non-responders to assist with long-term follow-up. Patients will be identified using only their unique trial number to verify identify on the data collection forms and in any correspondence between the FEMME study office and the participating site. Consent forms will be collected by the FEMME study office and stored securely in the trials master file. These forms will be available to various regulatory bodies for inspection upon request. These data will be entered onto a secure computer database, either directly by the local site via the internet using secure socket layer (SSL) encryption technology, or indirectly from paper forms by FEMME study office staff. Access control will ensure that local trials staff will only be able to view information relating to participants at their site.

Blood samples, which have been transferred from local centres to the University of Birmingham’s Human Tissue Repository will only be identified by a code containing the participant’s trial number, the treatment they were randomized to, the time-point at which the bloods were taken, and whether the samples were drawn on days two, three, or four of the participant’s menstrual cycle. Central laboratory staff will not have access to personal or clinical trial data.

All personal information received in a paper format for the trial will be held securely in locked filing cabinets in a safe haven office and treated as strictly confidential according to BCTU policies. All staff involved in the FEMME study, be they clinical, academic, or employees of BCTU, share the same duty of care to prevent unauthorised disclosure of personal information. No data that could be used to identify an individual will be published. Personal data recorded on all documents will be regarded as strictly confidential and will be handled and stored in accordance with the Data Protection Act 1998 and any amendments.

Ethical requirements: Multicentre ethical approval for the FEMME trial was granted by the Coventry and Warwickshire REC on 15 June 2011 (reference number: 11/WM/0149). The study will be performed in accordance with the principles stated in the Declaration of Helsinki [15]. Study procedures will be guided by the standards outlined in the Guidelines for Good Clinical Practice in Clinical Trials [16].

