## Methods/Design

### Study design

The FEMME trial is a randomised, open, multi-centre trial comparing UAE with myomectomy in women with symptomatic uterine fibroids.

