### Secondary outcomes

The FEMME trial’s secondary outcomes are:EuroQoL EQ-5D score and visual analogue scale score;Menstrual blood loss, assessed using the Pictorial Blood loss Assessment Chart (PBAC). This is a validated and well-used assessment of menstrual blood loss in women with uterine fibroids;Pregnancy outcomes - pregnancy will be reported by the woman in the first instance. The research nurse or trial coordinator will collect further information with respect to timing of pregnancy, biochemical pregnancy (positive pregnancy test), incidence of miscarriage, outcome of pregnancy, gestational age at delivery or miscarriage, complications of pregnancy, and labour;Adverse events - all adverse outcomes considered to be related to the study protocol or intervention will be collected. Since adverse outcomes may occur many months after intervention, these data will continue to be collected throughout the study;Length of hospital stay;Time to return to work or usual activity;Further treatment for incomplete removal or recurrence of symptoms, including hysterectomies;Ovarian reserve - blood samples will be taken from the women in each treatment arm for the measurement of the plasma levels of Anti-Müllerian hormone (AMH), a compound used as a proxy measurement of ovarian reserve, to determine if there is any difference at six weeks, six months, and twelve months post-procedure.

The time-points at which these follow-ups are performed are shown in Table 1.

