### Randomisation

In order to reduce bias as far as possible, following informed consent but before randomisation, the participant will be given the validated QoL questionnaires (the UFS-QoL and the EuroQoL EQ-5D) and asked to complete them. Once completed and returned to the clinical staff, the patient’s details will be entered onto a centralised online system which will allocate the patient to their treatment (myomectomy or UAE). A minimisation algorithm will be used to ensure that the groups are balanced as evenly as possible with respect to treatment group and also the following variables: the longest dimension of the largest fibroid (under 7 cm or over 7 cm), the number of fibroids present (1 to 3, 4 to 10, over 10), and if the woman desires pregnancy (yes or no).

The number and size of the fibroids present will be determined by imaging with either: magnetic resonance imaging (MRI) (contrast enhanced and/or non-contrast enhanced), ultrasound (vaginal or trans-abdominal), or hysteroscopy.

Should a participant have been randomised on any type of imaging other than MRI then, if local capacity allows, an MRI scan will be requested prior to the patient undergoing their procedure. After randomization, blood will be drawn into two BD Vacutainer® serum separator tubes (SST, BD, [name]) for the proxy measurement of ovarian reserve. These blood samples will be placed into a Royal Mail Safebox™ and sent to Birmingham University’s Human Tissue Repository. Upon receipt, the blood samples will be transformed into serum and stored in a secure biobanking facility at −80°C until analysis. Finally, the participant will be given a copy of the menstrual blood loss diary to take away with them and asked to complete it when they start their next period. Upon completion this blood loss diary will be returned to the trials office in a prepaid envelope provided.

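### The AMH sample code includes the randomised treatment, which sits in tension with the stated limit on laboratory access and serves no apparent purpose

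*Protocol article*

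**What the plan says.** Under Data management and quality assurance, Confidentiality, the protocol article states that samples sent to the Human Tissue Repository "will only be identified by a code containing the participant’s trial number". The list of code elements continues with "the treatment they were randomized to, the time-point at which the bloods were taken", and ends with whether the draw fell on cycle day two, three or four. The sentence after it reads "Central laboratory staff will not have access to personal or clinical trial data".

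The samples serve a between-arm comparison. Under Secondary outcomes, "blood samples will be taken from the women in each treatment arm for the measurement of the plasma levels of Anti-Müllerian hormone (AMH"), the proxy for ovarian reserve, at six weeks, six months and twelve months. The abstract adds a measurement before the procedure.

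On handling, the Randomisation section says "After randomization, blood will be drawn into two BD Vacutainer" tubes, and later "Upon receipt, the blood samples will be transformed into serum and stored in a secure biobanking facility" until analysis.

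On blinding, the Study design section says "The FEMME trial is a randomised, open, multi-centre trial comparing UAE with myomectomy in women with symptomatic uterine fibroids". The article neither promises nor rules out a blinded AMH assay.

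**The concern.** Which arm a woman was randomised to is, in ordinary usage, clinical trial data. If it forms part of the only identifier on a sample, then anyone who works with the sample by that identifier may be able to read it. That is hard to square with a sentence denying laboratory staff such data.

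The trial has to be open to women and clinicians, since it compares embolisation with surgery. Most other outcomes (questionnaires, bleeding diaries, return to work, further treatment) come from people who know what was done. AMH is the one listed secondary outcome read off a laboratory assay, so it is the easiest to shield from knowledge of the arm. The section on previous work says that the effect of embolisation on ovarian function is disputed and that the worry makes some clinicians reluctant to use it in women who may want to conceive. An AMH comparison is more persuasive, whichever way it falls, if the laboratory could not have known the arms.

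**Working it through.** No power, error rate or effect estimate enters this point, and the article gives no figure of its own to reproduce. The check is a comparison of passages followed by a count.

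**Is the treatment needed in the code?**
- The Confidentiality section calls the trial number unique and makes it the sole patient identifier on data forms and in correspondence between sites and the study office.
- The Randomisation section has treatment allocated by a central online system, so allocation is already held against each participant.
- Hence trial number plus time-point is enough to place any assay result in its arm at analysis. Cycle day may help in interpreting the sample. The treatment adds nothing to the linkage.
- The Data protection section limits staff to the electronic information their duties require. That rule does not cover tube labels, but a label showing the arm departs from its spirit.

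**Do the two adjacent sentences agree?**
- Sentence A: the sample's sole identifier includes the randomised treatment.
- Sentence B: central laboratory staff do not have clinical trial data.
- If allocation counts as clinical trial data and the code is legible to laboratory staff, A and B conflict. If B means only that staff cannot open the trial record or see personal details, both can stand, but the arm is still on the sample. The article does not say which is meant.

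**How many sample sets could carry the arm?**
- Input: target sample size 216 (Sample size section).
- Input: post-procedure AMH time-points, six weeks, six months and twelve months, so 3 (Secondary outcomes; Table 1, fertility potential row, taken here to be the AMH row because its follow-up points match).
- Post-procedure sets: 216 × 3 = 648.
- Baseline: the Randomisation section has blood drawn after allocation, so a baseline sample could carry the arm. Table 1 marks the baseline in the column before randomisation, when no allocation exists.
- With baseline included: 216 × 4 = 864. The difference, 864 − 648 = 216, depends entirely on which of these two places is right.
- Both totals are ceilings, since they assume that every woman gives every sample. They count samples exposed to the labelling rule and say nothing about the amount of bias.

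**The case against.** A reader might infer that the AMH laboratory is unblinded in breach of a blinding rule, and that the ovarian-reserve comparison is therefore biased. The article does not support that.

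- **Who sees the code.** The article describes how samples reaching the Human Tissue Repository are identified. It does not say who runs the assay, whether aliquots are relabelled first, or whether the treatment element is legible or encrypted. Such detail commonly sits in the full protocol or a laboratory manual, neither of which is shown. This stands: that assay staff would know the arm is an inference, though a direct one, because the code is the only identifier. Likewise, the absence of a reason means only that this article gives none.
- **What the access sentence promises.** It closes a section on confidentiality, and can be read as barring laboratory staff from personal details and the trial database. No passage promises a blinded assay. This stands in part: the passages are in tension and do not flatly contradict each other. The narrower reading is not what the wording says, however, and it would still leave the arm in the code.
- **Routes to bias.** Repeat assays, rejection of poor samples, values near a detection limit and batching by arm are all conceivable, but the article describes none of them. AMH is a measured concentration and not a rating. This stands: the routes are conjecture and their size cannot be calculated.
- **Reach.** AMH is one of eight listed secondary outcomes. The primary outcome, the two-year health-related quality-of-life score from the fibroid questionnaire, and the sample size built on it, are untouched. This stands and limits the severity.
- **The open design.** It explains why women and clinicians know the treatment. It gives no reason for the laboratory to know it, so this part of the objection fails.

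**Conclusion.** The point holds as a labelling rule that is badly fixed. The article puts the randomised treatment into the sole identifier of each stored blood sample, next to a sentence that reads as though laboratory staff should not have it, and the trial number makes the element redundant. As written, staff working from the code could know the arm for AMH.

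It reaches at most 648 sample sets if baseline blood precedes randomisation, and 864 if it follows. This rests on the code being legible to those who handle or assay the samples and on no relabelling beforehand, neither of which the article settles. Any effect on the AMH comparison cannot be quantified, and the primary outcome is not affected. Severity is moderate to low: a cheap safeguard for a secondary outcome on a disputed question, and not something that threatens the trial's main conclusion.

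**What to change.** - Remove the treatment from the sample code. Keep trial number, time-point and cycle day.
- Mask the treatment on samples already banked before they are assayed.
- Link assay results to allocation only in the trials office, after the results are final.
- Reword the two Confidentiality sentences so that they agree. If masking before assay is already in place, say so.
- Reconcile the Randomisation section with Table 1 on whether baseline blood is drawn before or after allocation.

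The cost is a new label template, plus modest work on stored tubes with some risk of mislabelling, which a second check against the trial number would limit. No patients or power are lost. The trial is still recruiting and serum is held until analysis, so the change is easiest now; samples assayed with the arm visible could be brought under masking only by re-assay.

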#### Monitoring of all types of adverse event

All types of adverse event which occur to participants in the FEMME trial will be reported as soon as possible after the clinician becomes aware of the event. An adverse events form should be completed as fully as possible and sent via fax to the trials office. This form will include an assessment of causality. Upon receipt, the trials office will log details of the adverse event on that patient’s record on the central trials database and forward an anonymised copy of the form to the sponsor and the Chief Investigator. Anonymised details of all adverse events will be presented to the DMC for scrutiny each time they meet. These anonymised details will be reported to the REC annually.

#### Trial Management Group

The Trial Management Group (TMG) is responsible for the overall design and conduct of the study, analysis of the data, and reporting and dissemination of results. It will act on the advice of the Trial Steering Committee (TSC), the DMC, and the funders (National Institute for Health Research Health Technology Assessment Programme [NIHR HTA]).

#### Data Monitoring Committee

The primary role of the DMC is to ensure patient safety and treatment efficacy whilst the trial is ongoing. At intervals specified by the DMC the senior trial statistician will provide confidential interim analysis of all available data, alongside anonymised reports of any adverse events suffered by participants in the trial. This will be reviewed by the DMC who will advise the TSC if the trial should continue as it is, continue with modifications, or be halted due to futility, safety concerns, or overwhelming benefit. The TSC will then decide whether to close or modify any part of the trial. Unless this happens then no one other than the trial statisticians (who supplied the confidential analysis) and the members of the DMC will be made aware of the results of the interim analysis.

The members of the FEMME DMC are: [name] (Chair; University of Oxford), [name] (Queens Medical Centre, Nottingham), and [name] (London).

### Trial status

The FEMME trial is currently recruiting.

## Abbreviations

AMH: Anti-Mullerian hormone
BCTU: Birmingham Clinical Trials Unit
DMC: Data Monitoring Committee
EQ-5D: EuroQol – 5D score and visual analogue scale score
GP: General practitioner
HMB: Heavy menstrual bleeding
HRQoL: Health-related quality of life
NHS: National Health Service
PBAC: Pictorial Blood loss Assessment Chart
PIS: Participant information sheet
QALY: Quality-adjusted life year
QoL: Quality of life
REC: Research Ethics Committee
SSL: Secure socket layer
TMG: Trial Management Group
UAE: Uterine artery embolization
UFS-QoL: Uterine fibroid symptom quality of life.
